## Abstract

**Background:**

Patellofemoral pain syndrome (PFPS), also known as Anterior Knee Pain, is a common cause of recurrent or chronic knee pain. The etiology is considered to be multifactorial but is not completely understood. At the current time the leading theory is that pathomechanics in the patellofemoral joint leads to PFPS. Traditionally, conservative treatment has focused on improving strength and timing in the quadriceps muscles. In recent years, evidence has been accumulating to support the importance of hip control and strengthening in PFPS. Two recent studies have shown promising results for hip strengthening as an isolated treatment for PFPS. The aim of this randomised contolled trial (RCT) is to compare isolated hip strengthening to traditional quadriceps-based training and a control group with free physical activity.

**Methods/Design:**

An observer-blinded RCT will be performed. We intend to include 150 patients aged 16–40 years, referred from primary care practitioners to the department of Physical Medicine and Rehabilitation in Kristiansand, Norway for PFPS with more than three months duration. Patients meeting the inclusion criteria will be randomised using opaque sequentially numbered sealed envelopes to one of three groups: isolated hip strengthening, quadriceps based training, or a control group (free physical activity). All groups will receive standardized information about PFPS formulated with the intention to minimize fear avoidance and encourage self-mastery of symptoms. Standardized exercises will be performed under supervision of a study physiotherapist once per week in addition to home training two times per week for a total of six weeks. The primary outcome measure will be the Anterior Knee Pain Score (AKPS) at three and 12 months. Secondary outcome measures will include Visual analogue scale (VAS) for pain, hip abductor and quadriceps strength, the generic EuroQol (EQ-5D), Hopkins Symptom Checklist (HSCL), Knee self-efficacy score and Tampa score for Kinesiophobia.

**Discussion:**

This trial will help to elucidate the role of hip and quadriceps strengthening in the treatment of PFPS. Information as to the role of anxiety and depression, kinesiophobia and self-efficacy will be collected, also as regards prognosis and response to exercise therapy.

**Trial registration:**

ClinicalTrials.gov reference: NCT02114294.

## Background

Patellofemoral pain syndrome (PFPS), also known as Anterior Knee Pain, can be defined as pain behind or around the knee cap (patella), provoked during loading of the knee in flexion or extension, in the absence of other specific pathology of the knee joint [1]. It is one of the most common causes of pain in the lower extremity, with the reported prevalence ranging from 7% to as high as 26%, although the true incidence and prevalence of PFPS have not been adequately studied [2-4]. Despite being commonly regarded as a benign and self-limiting condition, several long-term studies show that as many as 73-96% of patients with PFPS have continued pain longer than four years after diagnosis [5-8].

The etiology of PFPS is not completely understood, and is considered to be multifactorial [1,9]. The primary theory at the current time is that patellofemoral malalignment and maltracking (pathomechanics) result in PFPS [10]. Suggested mechanisms causing PFPS are overload, patellar maltracking/malalignment and imbalances in muscle strength and contraction [1,9,11,12]. Factors such as fear avoidance (kinesiophobia) and catastrophizing may be contributing factors [13-15]. Central neurological mechanisms such as sensitization or neuropathic pain also could be possible mechanisms influencing the pain experienced in some patients [16-18].

Several studies have underlined the importance of the quadriceps muscle function including timing and/or activity of the vastus medialis obliquus (VMO) [19-21] although the evidence is conflicting [22]. Traditionally, conservative treatment principles have therefore focused mainly on training strength, balance and timing in quadriceps muscles, especially VMO [1,23,24], often in combination with other modalities such as stretching, taping, and orthotics [1,23,25]. There is some evidence for a short-term effect of quadriceps-based training [23]. However, long term results after quadriceps-based training may be poorer, with up to 80% still reporting pain at five-year follow-up in one study [6].

In recent years there has become an increased focus on the importance of hip strength and control in PFPS. Several studies indicate that women with PFPS have altered hip kinematics during more demanding loading such as running, jumping and landing [26-28]. Studies using dynamic MRI suggest that increased femoral internal rotation results in increased lateral patellar displacement and resultant increased stress in the patellofemoral joint [29,30]. Women with PFPS have been found to be weaker in hip abduction and external rotation compared to healthy controls, although a recent systematic review raises the question as to the causality of the relationship [31,32].

More recent studies have reported promising results when strengthening hip abduction and external rotation on women with PFPS are used prior to [33], or in addition to [34-36], quadriceps-based training, and a recent systematic review concludes that proximal exercises are effective in treating PFPS [37]. A newly published large RCT compared quadriceps-based training to hip and core strengthening and found no significant differences in outcome, but an earlier effect of proximal exercises [38]. Posterolateral hip strengthening has only recently been studied as an isolated treatment for PFPS, and results are promising [39,40]. Much is still unclear regarding the role of proximal muscular strength and control in PFPS. Most published studies are relatively small and have methodological limitations. A newly published systematic review concludes with the need for more research to further evaluate the possible effects of different exercise therapy modalities on PFPS [41].

### Aims

The aim of this study is to compare the effect of isolated hip strengthening exercises, traditional quadriceps based exercises and free physical activity in patients with patellofemoral pain syndrome. The primary outcome is the Anterior Knee Pain Score (AKPS) at three months and one year. Our null-hypothesis is that there is no difference between the three groups for primary or secondary outcomes, measured at three months and one year.

## Methods/Design

### Trial design

This is an observer-blinded randomised controlled trial (RCT) with first primary endpoint at three months, and second primary endpoint at one year (Figure 1: diagram).

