#### Primary outcome measure

The main hypothesis in the present study will be examined at three and 12 months using the Anterior Knee Pain Scale (AKPS) as the primary outcome measure. This is a self-report questionnaire consisting of 13 questions to assess severity of pain and disability [46]. It has been validated for use in this patient population [47]. The categories within each question are weighted, and the responses are summed for an overall index where 100 represents perfect function and 0 represents worst possible function. The minimal clinically important difference (MCID) was reported to be 10 points in a previous study [47]. This questionnaire will be translated to Norwegian and validated according to standard scientific procedures with approval from Kujala et al. [46].

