### Sample size

The power and sample size calculations are based on a one-way Analysis of Variance (ANOVA) model at follow-up that does not take into account adjustment for the baseline values. Based on previous studies, standard deviation of AKPS and VAS is assumed to be 13.5 and 2.25, respectively. MCID for AKPS or VAS is set at 10 and 2, respectively [47]. With these assumptions 27 patients are required in each of the treatment groups (in total 81 patients for all three groups) to obtain 80% statistical power with 5% significance level for AKPS, and 19 in each group for VAS. To take into account possible missing data or drop-outs, a minimum of 35 patients will be included in each group. We will therefore include a minimum of 105 patients in total in this study but intend to include as many as 50 in each group (150 in total) to improve the power of the study considering the assumed heterogeneity of the study population.

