### Planned statistical analysis

All eligible patients, regardless of their compliance with the protocol (analysis by intention-to-treat) will be included in the main analysis.

To assess the primary endpoints of the study after three months and one year the differences between the three treatment groups will be analysed with an Analysis of Covariance model using the baseline value as one of the covariates. Assumptions of the model will be checked. To analyse the time course repeated measures will be analysed using linear mixed models. The influence of factors including compliance, muscle strength, psychological factors, joint hypermobility and baseline pain levels will also be examined with regard to treatment response.

A blinded statistical analysis and review of the outcome data is planned [62]. Only after the writing committee members have agreed that there will be no further changes in the interpretation, the randomisation code will be broken, and the manuscript of the final study will be published.

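### AKPS is primary at both three months and one year, but there is one 5% level and no stated rule for combining the two tests, and the null hypothesis also takes in the secondary outcomes

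*Protocol article*

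**What the plan says.** Four sections of the protocol article treat AKPS at two times as primary.

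- Aims: "The primary outcome is the Anterior Knee Pain Score (AKPS) at three months and one year".
- Trial design: "first primary endpoint at three months, and second primary endpoint at one year".
- Primary outcome measure: the main hypothesis is examined at three and 12 months, with AKPS as the measure.
- Planned statistical analysis: "To assess the primary endpoints of the study after three months and one year the differences between the three treatment groups will be analysed" by analysis of covariance with the baseline value as a covariate.

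The significance level appears once, under Sample size. The calculation is "based on a one-way Analysis of Variance (ANOVA) model at follow-up", and 27 patients per group are said to be needed "to obtain 80% statistical power with 5% significance level for AKPS". Neither the level nor the model refers to two endpoints.

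Aims words the null hypothesis as "there is no difference between the three groups for primary or secondary outcomes, measured at three months and one year".

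**The concern.** Two statements fixed in the article do not fit together.

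**Two primary tests, one level.** With two primary endpoints, the 5% level has a definite meaning only once the rule for success is known. If a difference at either time is enough and each is tested at 5%, the overall error exceeds 5%. If both are required, it does not. The article does not choose. The only sentence that bears on the choice is the null hypothesis in Aims: a statement of no difference at both times is false as soon as there is a difference at one.

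**Two versions of the hypothesis.** Aims puts the secondary outcomes inside the null hypothesis. The Primary outcome measure section limits the main hypothesis to AKPS, and the other measures are listed as secondary. The two definitions differ and need to be reconciled.

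At stake is the trial's headline claim. A difference at only one of the two visits could be reported as a positive primary result at 5% when the real error rate is higher. The sample size also depends on the rule, because a split level needs more patients than the 27 per group given.

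**Working it through.** **Inputs.** From Sample size: SD of AKPS 13.5, difference of interest 10, level 5%, power 80%, 27 evaluable per group, minimum enrolment 35 per group, intended enrolment up to 50 per group. From Trial design and Planned statistical analysis: three groups and two primary time points. Assumed, because the article gives neither: the pattern of the three group means, and the within-patient correlation of AKPS between visits.

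**Step 1: reproduce the stated sample size.** One-way ANOVA with three groups of n has noncentrality λ = n·Σ(mean − grand mean)²/SD², with 2 and 3(n − 1) degrees of freedom. For means (0, 0, 10), Σ = 66.67. With n = 27, λ = 27 × 66.67/182.25 = 9.88, and power at 5% is 79.4%. The exact calculation gives 28 per group for 80%. The article's 27 is therefore reproduced to within one patient, by a single 5% test at a single visit.

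**Step 2: error over two tests.** If the two visits were independent, the chance of at least one false positive at 5% each is 1 − 0.95² = 9.75%. The visits share patients, so the tests are correlated. Simulating 200,000 null trials per setting, with 50 per group and one three-group F test per visit:

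| Assumed correlation between visits | Either test positive, 5% each | Either test positive, 2.5% each |
|---|---|---|
| 0 | 9.7% | 4.9% |
| 0.3 | 9.6% | 4.9% |
| 0.5 | 9.3% | 4.8% |
| 0.7 | 8.4% | 4.3% |
| 0.9 | 7.2% | 3.7% |

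If both visits had to be positive, the error could not exceed 5% and no adjustment would be needed.

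**Step 3: power if a visit is tested at 2.5%.** With the formula of Step 1 at 2.5% and means (0, 0, 10), 80% power needs 33 evaluable per group, 99 in total, instead of 28. The step from 27 to 35 implies a loss of 8/35 = 23%. At that loss, 33 evaluable means 33 × 35/27 = 42.8, so 43 enrolled per group or 129 in total. That lies above the minimum of 105 and below the intended 150. With 50 enrolled, 50 × 27/35 = 38.6, so about 38 are evaluable.

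| Evaluable per group | Means (0, 0, 10): 5% / 2.5% | Means (0, 5, 10): 5% / 2.5% |
|---|---|---|
| 27 | 79.4% / 70.2% | 66.4% / 55.3% |
| 38 | 91.9% / 86.7% | 82.1% / 73.7% |
| 50 | 97.4% / 95.1% | 91.7% / 86.5% |

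These figures, like the article's, take no credit for adjustment for baseline.

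**The case against.** The strongest reply is that multiplicity rules are usually set out in a full protocol or analysis plan, and neither is shown. That stands for the detail: the absence of a testing procedure would not by itself be a finding in a journal article. It does not cover what the article does fix, namely two primary endpoints beside a single 5% level sized for one follow-up, and a null hypothesis in Aims that differs from the main hypothesis stated later.

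Four stronger readings are tempting, and the document does not support them.

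- *Each endpoint is planned at 5%.* This is an inference. The 5% occurs only under Sample size and is not assigned to each visit. The inflation is therefore conditional on an either-suffices rule with each test at 5%.
- *Any secondary outcome can carry the trial.* The wording in Aims literally allows it, but the Primary outcome measure section confines the main hypothesis to AKPS and the other measures are labelled secondary. An error rate computed over all the secondary tests would describe a procedure that the trial does not plan.
- *Pairwise comparisons will be run unprotected.* The Control group section makes clear that pairwise questions matter, but Planned statistical analysis specifies a comparison of the three groups and does not say that pairs are tested without it.
- *"First" and "second" primary endpoint already set a testing order.* The words follow calendar time. Nothing makes the one-year test depend on the three-month result.

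**Conclusion.** The concern holds in a limited form. The article's two primary endpoints and its null hypothesis do not, as written, hold the one 5% level that it states. If a difference at either visit counts and each is tested at 5%, the error over the two AKPS tests is about 7% to 9.75%. The upper end is the independence bound. The lower end assumes a correlation of 0.9, and the article gives no correlation. The conflict between the null hypothesis in Aims and the AKPS-only main hypothesis is a matter of wording and rests on no assumption.

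If a full protocol or analysis plan already sets a rule, the article's text only needs to be brought into line with it.

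**What to change.** 1. Restrict the confirmatory null hypothesis in Aims to AKPS, in agreement with the Primary outcome measure section, and describe the secondary outcomes as supportive.
2. State one rule for the two AKPS tests before the randomisation code is broken:
   - *Fixed sequence*: the three-group test at three months at 5%, then at one year at 5% only if the first is significant. No level is split and the sample size is unaffected. The cost is that no confirmatory one-year claim is possible if three months fails.
   - *Holm*: the smaller of the two p-values against 2.5%, and if significant, the other against 5%. Either visit can then succeed alone. The cost is power at the first step, as in the 2.5% columns above: 95.1% / 86.5% with 50 evaluable per group (one group differing / evenly spaced means), 86.7% / 73.7% with 38, and 70.2% / 55.3% with 27. The intended 150 patients can carry this if one group differs from the other two; the 27 evaluable behind the minimum of 105 cannot.
3. Test pairs of groups at a visit only after that visit's three-group test is significant. With three groups this protects the three pairs within that visit, at the level used there. It does not by itself hold 5% over all six pairs at both visits; if that is wanted, keep each visit at 2.5% throughout.

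The change takes a few sentences. A fixed sequence is the cheaper choice if three months is the main question, and Holm is preferable if a one-year claim must be able to stand alone.

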**Figure 1 Fig1:**
[figure not shown]
**Patient flow through the study.**

### Ethics

Ethics approval for this study has been received from the Ethics Committee Health Region Southeast, Norway.

### Participants

Participants will be recruited from general practitioners, chiropractors, manual therapists and from departments of orthopedic surgery, rheumatology and physical medicine and rehabilitation. To increase awareness of the trial, potential sources of referral will receive regular written information on the ongoing trial, and general practitioners will be invited to attend lectures on knee complaints with a focus on the current study.

All potential participants will be screened to determine their eligibility according to the following inclusion and exclusion criteria. For inclusion, patients should be 16–40 years of age and have at least three months history of peri- or retropatellar pain with worst pain intensity during previous week of VAS 3 or more. The pain should be provoked by at least two of the following activities: Stair ascent or descent, hopping, running, prolonged sitting, squatting or kneeling. On clinical exam, pain should be present during one of the following: Compression of the patella, palpation of the patellar facets. In patients with bilateral pain the worst knee will be included, and presence of bilateral pain will be documented. One specialist in Physical Medicine and Rehabilitation (PM&R) will perform clinical examinations of all patients. Possible candidates will have a plain x-ray and MRI of the knee joint performed, if this has not already been performed within the previous six months.

Exclusion criteria include clinical, x-ray and MRI findings indicative of meniscal or other intra-articular injury, injury to or increased laxity of cruciate or collateral ligaments, or other pathology including: osteoarthritis, Osgood-Schlatter or Sinding-Larsen-Johanssen syndrome, jumpers knee, or of significant knee joint effusion, significant pain from hip or lumbar spine on clinical evaluation, with potential for causing referred pain to the knee, or hindering the patient’s ability to perform the prescribed exercises, recurrent patellar subluxation or dislocation, previous surgery to the knee joint, NSAID or cortisone use over an extended period of time, having suffered trauma to the knee joint judged during clinical evaluation to have a significant effect on the presenting clinical condition. Patients having received physiotherapy or other similar treatment for patellofemoral pain syndrome within the previous three months will also be excluded.

### Randomisation

Patients who fulfill the inclusion criteria and consent to take part in the trial after they have received the standardized oral and written information, will be randomized to receive hip strengthening (H), quadriceps-based training (Q), or control group (C). Sealed opaque randomization envelopes with a study-specific patient number will be supplied by an external statistician. The randomization sequence is computer-generated with randomization blocks of a variable size which is unknown to any of the research team. A nurse not otherwise involved in the research study will take the sealed opaque numbered envelopes in order, by number, and deliver the correct envelope to the treating physiotherapist. The envelope contains a piece of paper which is labeled with the same patient specific number, plus the group assignment (H, Q or C). The group assignments will be communicated for the purpose of data analysis in coded form. The code will only be revealed when the data analysis is complete.

### Interventions

#### Standardized information

All groups receive standardized oral and written information from the Physical Medicine and Rehabilitation (PM&R) specialist at the time of inclusion to the study focusing on understanding of the etiology of PFPS, and especially reassurance as to the benign nature of the condition. The information is formulated with the intention to minimize fear avoidance and encourage self-mastery of symptoms. Advice will be given to stay physically active without excessively provoking knee pain, and types of potential activities will be explored with the patient. Participants will be asked to refrain from seeking other forms of treatment (eg. physiotherapy, shoe inserts, injections, laser, etc.) during the study. The same written and oral information will be repeated by the study physiotherapists at randomization. Standardization of information will be achieved by regular meetings for the research staff before initiation of the study and throughout the study period.

#### Hip strengthening protocol

The hip strengthening exercises consist of side-lying hip abduction, hip external rotation (clam-shell) and prone hip extension. The exercise positions are based on previous studies of hip strengthening [34,39,40], and are chosen to maximally isolate the hip abductors and external rotators, respectively. Initial dosage of 10 × 3 will be used, with a progression up to a maximum 20 × 3, as previous studies on isolate hip strengthening have used a high-repetition approach [39,40], which is also supported by studies examining dose–response relationship in PFPS exercises [42]. Additional resistance will thereafter be provided by weights or elastic tubing if necessary. One session per week will be performed under supervision of the physiotherapist, with two additional sessions performed as home sessions, for a total of three sessions per week. To avoid focus on pain and pain behaviours, dosage will be adjusted on an individualized basis once weekly by the physiotherapist according to level of function, based on principles for operant conditioning [43]. This entails setting quotas of exercise below the patients’ limit of tolerance as opposed to training up to the pain threshold. A dosage will be chosen in which the last repetitions are difficult while still allowing the patient to maintain high quality of movement control throughout the entire program.

